### Randomization

A total of 200 enrolled patients will be scheduled for renal angiograms to confirm the anatomical suitability of their renal arteries. A stratified block randomization of patients to receive cryo-RDN or the sham procedure will be performed at a ratio of 1:1 according to study site. To minimize the human factors, the allocation will remain concealed until the patients are anesthetized in the interventional lab. In addition, patients allocated to the sham group will be anesthetized for 30 min in the same manner as those undergoing cryo-RDN.

### Interventions

Eligible patients will undergo either cryo-RDN with Cryofocus system or dual renal angiography only. It is expected that their previously prescribed standardized antihypertensive drugs will remain unchanged in the 6-month follow-up period after the intervention.

However, if in the first 3 months after the intervention a patient experiences dizziness, fatigue, or other symptoms of hypotension, or after 4–6 months the patient has office SBP < 100 mmHg and office DBP<50 mmHg, then the investigators can decrease the number or the dosage of the antihypertensive drugs. Moreover, additional drugs can be added at 4–6 months if a patient taking two or three types of standard antihypertensive drugs has office BP>160/110 mmHg or if a patient taking four types of standard antihypertensive drugs has office BP > 180/110 mmHg (the rules for adjusting dosages are listed in Additional file 2: Table S2).

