#### Inclusion criteria at the first screening visit

Patients must meet all the following criteria:
Patient is ≥18 and <75 years old at the time of randomization.Patient has continually taken antihypertensive drugs ≥3 months.Patient agrees to cooperate with all study procedures.Patient provides written informed consent to participate in this clinical study.

In addition, the patient must meet one of the following conditions:
Patient is currently on two or three types of antihypertensive drugs with 150 mmHg ≤ office SBP ≤ 180 mmHg and office DBP ≥90 mmHg.Patient is currently on four types of antihypertensive drugs with office SBP ≥140 mmHg and office DBP ≥ 90 mmHg.Patient has been on five types of antihypertensive drugs for ≥3 months, and office SBP ≥140 mmHg, office DBP ≥ 90 mmHg, and 24-h SBP ≥135 mmHg.

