## Discussion

This study was designed to assess the safety and efficacy of cryo-RDN using Cryofocus balloon catheters in patients taking polypharmacy with uncontrolled hypertension.

The short-term safety of this cryo-RDN device has been verified in healthy swine. Plasma norepinephrine and RAS (renin angiotensin system) levels were blunted, and SBP (systolic blood pressure) had declined 28 days after cryoablation. No major restenosis occurred in the renal artery, and the sympathetic nerves peripheral to the renal artery exhibited necrosis and perineurial fibrosis [8]. In addition, recent results from the First-in-man study also showed that the mean ambultory blood pressure reduction was 11.8/8.0 mmHg at the 6-month follow-up of six patients with uncontrolled hypertension. Based on these results, we focused on the safety and efficacy in the longer term for a larger population. RDN has only been carried out internationally for 10 years and large clinical studies of this device-based method have had inconsistent results. So far, the longest trial follow-up was 36 months in HTN-1 and HTN-2. The average office SBP reduction was 21–33.6 mmHg and there was a 53–85% response rate, demonstrating the long-term sustainability of RDN in BP reduction [11, 12]. The global boom in RDN research suffered a setback with the negative results from HTN-3 [13, 14]. However, poor drug adherence, isolated systolic hypertensive patients, and inexperienced operators may have distorted the results [15, 16]. A more rigorous study design is needed. As recommended by European Society of Hypertension, ambulatory BP is of more prognostic value than office BP, which may be confounded by white coat hypertension and other factors [17]. The positive results of HTN-OFF MED have again validated the effectiveness of RDN regardless of which antihypertensive drugs are taken [7]. Results from HTN-OFF MED, HTN-ON MED, and Radiance SOLO were published this year. These trials had a 24-h SBP primary endpoint. BP reduced by an equivalent of less than 10 mmHg. Thus, the antihypertensive effect and safety of RDN are widely accepted [6, 18].

Statistics have shown that the hypertension control rate in China was only 13.8% in 2012 [10]. This low rate is not satisfactory and there are limitations to drug treatment.

The following conclusions can be drawn:

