The antihypertensive effect of RDN can be maintained for days, and there appears to be no fluctuations due to metabolic effects unlike pharmacological therapy.The antihypertensive effect of RDN is effective long term and does not depend on drug adherence.The antihypertensive effect of RDN does not conflict with drug action, and it is not offset by whether patients are taking medication.

However, to our knowledge, almost all large clinical studies have used individuals from Europe and America as research objects. No trial published so far includes China. In addition, most RDN studies are radiofrequency-based or ultrasound-based. To date, there was only one study reported great antihypertensive effect of cryoablation RDN on non-responders to radiofrequency ablation. But that was using atrial fribrillation ablation catheter as a remedy. [3]. Clinically, cryoablation has been widely used in therapies for cardiac disease and tumors [19, 20]. The formation of intra- and extracellular ice crystals and vascular stasis develop shortly after thawing, which results in cell and tissue death. Thus, cryoenergy was adapted to destroy hyperactivated sympathetic nerves. Previous animal experiments have revealed that (1) cryoablation is more penetrating than radio waves, resulting in fewer (neurofilament light)-positive nerves remaining [21, 22], (2) cryoenergy is more protective and friendlier to peripheral tissues than radio waves in arrythmia ablation [23–26], (3) radiofrequency catheters ablate lesions circumferentially but the lesions vary in shape, area, and diameter depending on the adjacent tissue substructures. Based on these potential advantages, we constructed a special cryoablation balloon with a spherical ablation pattern.

Therefore, we will focus on the safety and efficacy of cryo-RDN in the Chinese population. The aim is to provide a new way to improve the control of hypertension in China as a complement to drug therapy.

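### Symptoms of hypotension permit drug reduction only in the first 3 months; at 4–6 months the only printed trigger is office SBP <100 and office DBP <50 mmHg together

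*Protocol article*

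**What the plan says.** The rule is in the Interventions section of the protocol article. The default is: "It is expected that their previously prescribed standardized antihypertensive drugs will remain unchanged in the 6-month follow-up period after the intervention".

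Two grounds for reducing the number or dose of drugs follow:

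- **Early:** "in the first 3 months after the intervention a patient experiences dizziness, fatigue, or other symptoms of hypotension". No BP limit is attached.
- **Late:** "or after 4–6 months the patient has office SBP < 100 mmHg and office DBP<50 mmHg". Symptoms are not named, and the two limits are joined by *and*.

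If either ground is met, the investigator may reduce treatment. The same paragraph covers drug additions at 4–6 months and refers to Table S2 in Additional file 2 for how dosages are adjusted. That table is not shown. No other section gives a ground for reducing drugs; the Withdrawal section deals with leaving the study, not with changing a dose.

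**The concern.** Hypotension is a foreseeable harm when a BP-lowering device is added to fixed multi-drug therapy. The printed rule treats the same patient differently on either side of month 3, and the article does not say why.

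Its own premises give no ground for expecting the risk to end then. The Discussion states: "The antihypertensive effect of RDN is effective long term and does not depend on drug adherence". It also reports the first-in-man result at 6 months: "the mean ambultory blood pressure reduction was 11.8/8.0 mmHg at the 6-month follow-up of six patients with uncontrolled hypertension".

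The late BP limits do not replace the symptom ground, because both pressures must be very low at once. The Study visits section schedules post-discharge visits at 1, 3 and 6 months only, so no office BP is planned between months 3 and 6. Symptoms are what a patient can report in that interval, and they are what the late rule drops. What is at stake is a clear, uniform safety rule across 13 centers for the second half of follow-up.

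**Working it through.** There is no stated figure to reproduce. The check applies the printed rule to example patients and then asks how far BP must fall to meet the late limits.

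**1. The rule applied.** I read the late ground as covering months 4–6, in line with the next sentence on drug additions. The BP values are illustrative.

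| Patient | Month | Condition tested | Met as printed? |
|---|---|---|---|
| Symptoms, 88/58 | 2 | symptoms | yes |
| Symptoms, 88/58 | 5 | 88 <100 true; 58 <50 false | no |
| Symptoms, 105/65 | 5 | 105 <100 false; 65 <50 false | no |
| 88/45 | 5 | 88 <100 true; 45 <50 true | yes |

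Replacing *and* by *or* brings in 88/58 in month 5 but not 105/65. Letting symptoms count throughout brings in both.

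**2. The fall needed to meet the late limits.** Baseline is the second screening visit (Study patients), so its entry floors are the relevant ones.

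- Two or three drugs, floor 150/90: SBP fall above 150 − 100 = 50 mmHg, and DBP fall above 90 − 50 = 40 mmHg.
- Four drugs, floor 140/90: SBP fall above 140 − 100 = 40 mmHg, and DBP fall above 40 mmHg.
- Five drugs: no BP floor is printed at the second visit. The first-visit floor is 140/90, which would give 40 and 40 mmHg, but this is not a baseline figure.

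**3. Set against the falls that the article cites.** These comparisons are for orientation only.

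- For earlier trials of RDN the Discussion says: "The average office SBP reduction was 21–33.6 mmHg". At the upper end, a patient entering at 140 would reach 140 − 33.6 = 106.4 mmHg, still above 100.
- The first-in-man mean fall was 11.8/8.0 mmHg. The ratios are 40/11.8 = 3.4 and 50/11.8 = 4.2 for SBP, and 40/8.0 = 5.0 for DBP. They set an individual office fall against a mean ambulatory fall in six patients. A mean says little about the tail, where hypotension occurs.

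**4. Possible cost to the primary comparison.** All inputs here are assumed except the 8 mmHg design difference (Sample size calculation). Suppose 1 to 5 of 100 active-arm patients have drugs reduced, each rises by 10 mmHg, and none in the sham arm do.

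- 1/100 × 10 = 0.1 mmHg; 0.1/8 = 1.25%
- 5/100 × 10 = 0.5 mmHg; 0.5/8 = 6.25%

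**The case against.** **Table S2 is unseen.** A journal article condenses the full protocol, and Table S2 might contain a late symptom rule or settle *and* versus *or*. This lowers confidence. It does not remove the point: the article cites the table for adjusting dosages but states the triggers itself, and it assigns a different one to each period. That is a rule as printed, not a detail left out.

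**The wording is permissive.** Drugs are *expected* to stay unchanged, and investigators *can* reduce them. A reader might infer that the protocol forbids relieving symptomatic hypotension in months 4–6. The text does not support that. It only leaves such a patient outside the stated grounds. Drug changes are also anticipated elsewhere: patients needing an adjustment are described under the secondary outcomes, and adjustments enter the mixed model.

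**The phrase may be loose.** The joined limits could be prose for a paired threshold, like the 160/110 used for additions. That is possible, but changing *and* to *or* would still leave symptoms uncounted after month 3.

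**The size is uncertain.** A reader might also infer from the 40–50 mmHg falls and the ratios above that the late trigger is practically out of reach. The documents do not show this. Five-drug patients have no printed floor at baseline, and averages do not describe individuals. The same figures suggest that few patients would reach SBP <100 at all.

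**An objective limit guards against bias.** The trial is single-blinded, and dizziness and fatigue are non-specific. A purely subjective ground close to the 6-month primary endpoint could allow drug changes influenced by knowledge of allocation. The article does not offer this as its reason, but the point stands and should shape the fix.

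**Conclusion.** The point holds on the printed text. Symptoms of hypotension are a ground for drug reduction in the first 3 of the 6 months for which drugs are expected to stay fixed. At 4–6 months the only printed ground is office SBP <100 and DBP <50 mmHg together. A patient with symptomatic hypotension at 88/58 in month 5 meets no stated trigger.

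The conclusion rests on the article's wording, on reading the late ground as months 4–6, and on Table S2 not saying otherwise. Few patients are likely to be affected. No rate of symptomatic hypotension is given, so the number cannot be stated. This is a badly fixed safety rule that is worth correcting; it is not a prohibition on treatment and no threat to the trial's validity.

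**What to change.** In the Interventions section and in Table S2:

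1. Let symptomatic hypotension permit drug reduction at any time in the 6-month follow-up, with an office BP measured and the reason recorded at the time.
2. Change the 4–6 month limits to office SBP <100 mmHg **or** office DBP <50 mmHg, as a route for patients without symptoms.
3. Make Table S2 match.

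The edit is small, and the Trial status section says recruitment had not begun at submission. No scheduled visit is added, although a patient with symptoms between months 3 and 6 would need an unscheduled office reading.

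The downside is a few more late drug reductions, probably more in the active arm. On the assumed inputs above, this dilutes the BP difference by 0.1–0.5 mmHg, about 1–6% of the 8 mmHg design difference. Because the trial is single-blinded, some room also remains for changes influenced by knowledge of allocation. The BP reading and the recorded reason limit this and allow late reductions to be reviewed by arm.

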### Cryo-RDN procedure

Angiography and cryo-RDN procedures will be performed through the femoral artery by one or two designated interventionists at each study site after a combined training session. Under general anesthesia, a 10F sheath and a 6F Judkins Right (JR4.0) catheter will be inserted through femoral access into the renal arteries, and angiography will be performed on dual renal arteries to confirm anatomic feasibility and ablation sites. Intraprocedural anticoagulation will be administered with 100 units of heparin per kg. After randomization based on computer-generated random numbers, patients in the sham arm will be maintained under anesthesia for another 30 min. For patients in the cryo-RDN arm, the 6F catheter will be removed and, according to angiography, properly sized cryoablation balloons will be advanced to the distal segment of the main renal artery through an 8F guidance catheter and a 0.018″ SV-5 guide wire (Cordis, Johnson & Johnson, North West, Florida, USA). During the cryoablation procedure, the regional renal blood flow will be blocked for approximately 5 min on each side with cooling (average −95 °C, ranging between –115 and –80 °C) and rewarming. If needed, the cryoablation balloon catheter will be withdrawn and placed in a catheter of the right size for ablation on the other side of the renal artery. In addition, a bifurcation with a diameter ≥3.0 mm will also be additionally ablated, as a recent expert consensus suggests that this gives better clinical outcomes [7]. A final renal angiography will check that there is no renal artery obstruction, perforation, or dissection. The delivery system and sheath will be removed. Hemostasis of the femoral access site will be achieved using standard techniques.

### Study visits

A total of four visits will be scheduled for participants after the intervention, which will occur before hospital discharge and at 1, 3, and 6 months after discharge. At baseline and at all four visits, a clinical and biochemical evaluation will be undertaken and office BP and 24-h ambulatory BP will be measured. Another renal angiography will occur at the 6-month follow-up. At the 1-month visit, patients will be considered as outpatients and informed of their subsequent drug prescription. The other two follow-ups will require hospitalization.

### Outcome measures

The primary outcome of this study is the difference in the change in 24-h SBP from baseline to 6 months between the cryo-RDN treatment arm and the sham treatment arm. At each participating site, one or two staff members from the laboratory department, and not the clinical department, will be allocated to undertake the 24-h BP measurements during the study period.

The secondary outcomes are as follows:
Difference in change in 24-h SBP (daytime and nighttime) from baseline to 6 months between the cryo-RDN treatment arm and the sham treatment armDifference in change in 24-h SBP (daytime, nighttime, and 24-h) from baseline to 6 months between the cryo-RDN treatment arm and the sham treatment armDifference in change in office BP (SBP and DBP) from baseline to 6 months between the cryo-RDN treatment arm and the sham treatment armCharacteristics of patients who required an adjustment to their medication after the interventionAdherence of patients to taking their antihypertensive drug based on the eight-item Morisky Medication Adherence ScaleOperational performance evaluation of the test device in the cryo-RDN treatment armSide effects possibly caused by the test deviceMajor adverse eventsOther adverse events

Safety endpoints primarily include any adverse incidents, including but not limited to puncture-related vascular injury, renal artery complications, renal complications, systematic reactions and a change in renal function, which may be caused by the test device or other factors.

### Sample size calculation

PASS 13 was used to estimate the sample size. This trial was designed to compare the difference in 24-h SBP as a change from baseline to 6 months between the cryo-RDN treatment arm and the sham treatment arm. Based on data from previous studies, we chose a sample size of 81 per treatment arm. The between-group comparison will be powered at 95% to establish the superiority of cryo-RDN for the primary endpoint at a single-sided significance level of 0.025, considering a true 24-h SBP difference as 8 mmHg with a common standard deviation of 18 mmHg. Given an estimated dropout rate of approximately 20%, we increased the sample size to 100 per arm for a total of 200 participants.

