### Statistical analysis

The statistical analysis plan will be developed and performed by independent statisticians from the data monitoring committee. SAS software V.9.4 (SAS Institute, Cary, NC) will be used for the statistical analysis. Based on the intention-to-treat principle, the full analysis set and per protocol set will be adopted as the primary analysis populations. A two-sided *p* < 0.05 will indicate significance in all statistical tests. Appropriate descriptive indicators and hypothesis testing methods will be selected cautiously. Data, including demographics, baseline characteristics, and safety, will be summarized by treatment arm.

The primary efficiency outcomes are powered by a superiority test to detect the change in 24-h SBP from baseline to 6 months after the intervention. The sensitivity analysis will have a stratifying variable center as a fixed effect of an analysis of covariance (ANCOVA). A BP reduction will be tested by paired *t*-tests with 95% confidence intervals for the differences between treatment arms. Other categorical data will be tested using either Pearson’s χ^2^ test or Fisher’s exact test. Rank data will be tested by either the Wilcoxon rank sum test or the Cochran–Mantel–Haenszel test. Mixed-model repeated measures analysis including terms for the baseline measurement, types of drugs taken, and medication adjustments during the follow-up will be used for the reduction in BP.

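### The stated 95% power does not follow from the stated inputs: 81 per arm, 8 mmHg, SD 18 mmHg and one-sided 0.025 give 80%

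*Protocol article*

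**What the plan says.** The section Sample size calculation of the protocol article gives a complete set of inputs for the primary endpoint.

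- Comparison: the aim is to "compare the difference in 24-h SBP as a change from baseline to 6 months between the cryo-RDN treatment arm and the sham treatment arm".
- Size: "we chose a sample size of 81 per treatment arm".
- Power: "The between-group comparison will be powered at 95% to establish the superiority of cryo-RDN for the primary endpoint".
- Significance level: "at a single-sided significance level of 0.025".
- Effect and variability: "considering a true 24-h SBP difference as 8 mmHg with a common standard deviation of 18 mmHg".

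The number is then raised to 100 per arm (200 in total) for a dropout of about 20%. Allocation is 1:1 (section Randomization). The section Statistical analysis says that a two-sided p below 0.05 "will indicate significance in all statistical tests". For a superiority test in one direction this matches one-sided 0.025, so the two sections do not conflict on alpha. The article states no superiority margin, interim analysis or variance reduction for the calculation.

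**The concern.** The standardised difference is 8/18 = 0.44. With about 80 patients per arm, an effect of that size is usually associated with 80% power. A claim of 95% at the same size suggests that one of the published figures is wrong.

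The power figure tells ethics committees, investigators and readers how likely the trial is to miss the effect it was designed to find. That matters here because patients in both arms undergo an invasive procedure under general anesthesia, and because the Discussion describes earlier large trials of renal denervation as inconsistent, with a setback after one negative result. If this trial is neutral, a reader who believes the 95% would take it as strong evidence against an 8 mmHg effect. The design as described does not support that reading.

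**Working it through.** **Inputs** (all from the protocol article): n = 81 per arm, difference δ = 8 mmHg, SD σ = 18 mmHg, one-sided α = 0.025, 1:1 allocation. The superiority margin is taken as 0 because none is stated.

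**1. Power from the stated inputs.**

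Standard error of the difference = σ√(2/n) = 18 × √(2/81) = 2.828 mmHg.

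δ/SE = 8/2.828 = 2.828.

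Normal approximation: power = Φ(2.828 − 1.960) = Φ(0.868) = 0.807.

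Exact two-sample t-test (noncentral t, 160 degrees of freedom): power = 0.803.

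The stated 95% is not reproduced.

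**2. Sample size from the stated inputs.**

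n per arm = 2(z₁₋α + z₁₋β)²(σ/δ)², where (18/8)² = 5.0625.

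- 80% power: 2 × (1.960 + 0.842)² × 5.0625 ≈ 79.5
- 90% power: 2 × (1.960 + 1.282)² × 5.0625 ≈ 106.4
- 95% power: 2 × (1.960 + 1.645)² × 5.0625 ≈ 131.6

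| Power | n per arm, normal | n per arm, exact t | Enrolled per arm at 20% dropout (exact n/0.8, rounded up) |
|---|---|---|---|
| 80% | 80 | **81** | 102 |
| 90% | 107 | 108 | 135 |
| 95% | 132 | 133 | 167 |

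The plan's 81 is the exact-t answer for 80% power. The sample size, difference, SD and alpha therefore fit together, and the 95% is the figure that does not fit.

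**3. Power at other plausible numbers analysed (exact t).**

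- 80 per arm (100 less 20%): 79.8%
- 100 per arm (no loss at all): 87.8%

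**4. What would make 95% true with 81 per arm (exact t).** Either an SD of 14.0 mmHg with the difference kept at 8, or a difference of 10.3 mmHg with the SD kept at 18.

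**5. Other readings tried.**

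| Reading | Power | Why it fails |
|---|---|---|
| One-sided α = 0.05, 81 per arm | 88% | Misses 95% and contradicts the stated 0.025 |
| One-sided α = 0.05, all 100 per arm | 93% | Same |
| 162 taken as the number per arm | 97.9% | Contradicts 81 per arm |
| 200 taken as the number per arm | 99.3% | Same |
| Paired or one-sample t-test, n = 81 | 97.7% | Not a between-arm comparison; 95% would need only 68 |
| Baseline adjustment with correlation 0.63 (residual SD 18√(1 − 0.63²) ≈ 14.0) | 95.2% | Neither the adjustment nor the correlation is stated |

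**The case against.** Four points can be made on the other side.

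- **Another input may be the wrong one.** The article attributes its assumptions only to earlier studies, so the text alone cannot exclude an intended SD near 14 mmHg or a difference near 10.3 mmHg. This stands as a limit on what can be known. The exact match at 80% makes the power figure much the likeliest slip, and the fix below allows for either.
- **Covariate adjustment could lift the power.** The Statistical analysis section plans a mixed model with the baseline measurement, and a correlation of about 0.63 would bring 81 per arm to about 95%. But the sample size section gives 18 mmHg simply as the common SD and mentions no adjustment. The planned analysis may do better than 80%, but that does not make the published statement correct.
- **The miss rate may be below 20%.** If all 100 per arm are analysed, it falls to about 12%. A neutral result would also normally be judged on its confidence interval, which the article plans to report. Both points soften the consequence. Neither brings the miss rate down to 5%.
- **The trial remains sound at 80%.** This is a conventional level and type I error is unaffected. That is true, and it is why the correction can be small.

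The absence of a separate analysis plan does not help either. The article gives all the inputs itself, and no later document can make them yield 95%.

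**Conclusion.** The concern holds. With the inputs as published, power is 80.3% and not 95%, a gap of about 15 percentage points. The type II error is 19.7% against an implied 5%, about four times as large. The result assumes an unadjusted two-sample t-test, a superiority margin of zero and 81 evaluable patients per arm. With 80 or 100 evaluable per arm it moves only between 79.8% and 87.8%. The document does not show whether the 95% is a reporting slip or a planning error, but the sentence cannot stand as written.

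**What to change.** Restate the power as 80% for 81 evaluable patients per arm, with the difference, SD and alpha as given, and keep the total at 200. A 20% loss from 100 leaves 80 per arm and 79.8% power, so the 80% statement still describes the trial fairly.

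If the calculation actually used a different SD or difference, correct that input instead, give its source and show that it reproduces 81 per arm at 95%. If baseline adjustment was assumed, state the correlation and justify it.

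If 95% power is truly intended with the published inputs, the trial needs 133 evaluable per arm. That is 133/0.8 = 166.25, so 167 enrolled per arm and 334 in total, or 134 more than planned.

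The first option costs one corrected figure in the protocol, and in any registry or ethics text that repeats it (the article does not show whether one does). It needs no extra patients, though the stated power becomes less favourable. The article says recruitment had not begun at submission; if that is still so, the correction can be made before any patient is enrolled.
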